#### Qualitative analysis

Semi-structured interviews with key stakeholders will be audio recorded, professionally transcribed and analysed thematically using NVivo 12 software (QSR International). Two researchers will follow the six steps of thematic analysis outlined by Braun and Clarke [48]: familiarization, code generation, combining codes into themes, reviewing themes, determining significance of themes, and reporting findings. The researchers will independently code all of the transcripts and then meet to consolidate a shared codebook and seek feedback from the research team, including about any disagreements over codes. This codebook will be applied to coding the transcripts afresh, dividing the transcripts between the researchers. The researchers will then cluster codes into candidate themes. This will be presented to the research team to resolve any disagreements, determine the final themes, and discuss the significance and priority of themes for the study.

##### AIM 2—evaluation of the ENJOY Seniors Exercise Park on physical activity and wellbeing

Summary statistics will be used to describe the demographic, socioeconomic, equipment usage and health-related characteristics of Seniors Exercise Park area users at each time point. Data will also be examined and reported relative to the adult general public, based on the distribution of age, marital status, and country of birth (using Australian Bureau of Statistics census data for each local government area). Linear and logistic regression models (with main effects for site, time-point, season and their interaction) will be used to examine the impact of the implementation intervention on physical activity level (primary outcome) and other health user characteristics. Statistical significance of the interaction term will be used to determine if the outcome varied between sites at each intervention time point (I1-I3) or M1 relative to their baseline difference.

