#### Study setting and partners

In this study, five councils (six parks/sites) will participate in the project (four in metropolitan Melbourne and one in regional Victoria, Australia), including: City of Whittlesea (metropolitan), Nillumbik Shire Council (metropolitan), Hobsons Bay City Council (metropolitan), Wyndham City Council (metropolitan), and Mitchell Shire Council (two sites in regional Victoria). The proportion of the older population among these five local government ranges between 10.9% to 22% (people 60 years and over) and 7.4% to 17% (people 65 years and over) [26].

The design of the project aims for implementation in staggered stages of commencement in the following order: Barry Rd, Thomastown (City of Whittlesea); Andrew Pocket Park, Eltham (Nillumbik Shire Council); Donald Mclean Reserve, Spotswood (Hobsons Bay City Council); Central Park, Hoppers Crossing (Wyndham City Council); The Elms Reserve, Kilmore; and Chittick Park, Seymour (Mitchell Shire Council). Details of each park location, features and the surrounding areas are provided in Table 1. The locations of the metropolitan parks are spread as follows: 15–20 km north and north-east of the Melbourne Central Business District (CBD) (Thomastown and Eltham), 7 km south-west of Melbourne's CBD (Spotswood) and 24 km south-west of Melbourne's CBD (Hoppers Crossing). The two regional sites are located 65-104 km north of Melbourne (Kilmore and Seymour respectively).

**Table 1 Tab1:** Parks amenities and features

Amenities /features	Barry Road Community Activity Centre, Thomastown	Park Andrew Pocket Park, Eltham	Donald Mclean Reserve, Spotswood	Central Park Community Centre, Hoppers Crossing	The Elms Reserve, Kilmore	Chittick Park, Seymour
Within Seniors Exercise Park area						
Seniors Exercise Park equipment	Yes	Yes	Yes	Yes	Yes	Yes
Table and seats	2 benches, 1 × picnic table with chairs	2 benches, 1 × picnic table with chairs	1 bench	2 benches, 1 × picnic table with chairs	1 bench, 2 × picnic tables with chairs	2 benches
Shade Sail	Yes	Yes	No	Yes	No	No
Surrounding area adjacent to the Seniors Exercise Park						
Sport play court/field (e.g. oval/basketball/tennis court/netball)	Tennis court	Tennis court, mini-basketball court	Football oval	Pétanque	No	Football ovals
Water fountain	No	Yes	Yes	No	No	Yes
Public Toilet	No	Yes	Yes	No	No	No
BBQ / Picnic area	Yes	Yes	Yes	Yes	Yes	Yes
Seated benches	Yes	Yes	Yes	Yes	Yes	Yes

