#### Inclusion criteria

For the observational data collection, all park visitors during park observation periods will be included in the data recording.

For the face-to-face intercept survey at the park during the park observation periods, the following inclusion criteria will be applied: (1) adults aged 60 and over, (2) adults who are able to understand basic English and have conversational English.

For the semi-structured interviews for the contextual factors influencing the implementation, the following inclusion criteria will be applied: (1) key stakeholder representatives—council staff within the division (or equivalent) that are responsible or involved with the Seniors Exercise Park management/coordination/activation; community health/leisure centre managers/coordinators within the participating municipalities; (2) leaders of delivery programs (seniors group leaders, allied health professionals, exercise instructors) who utilise the Seniors Exercise Park as part of their program/service delivery.

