#### Exclusion criteria

The following exclusion criteria will be applied for the face-to-face intercept surveys at the park: (1) participants who identify themselves as less than 60 years of age and (2) who are unable to understand basic conversational English.

The following exclusion criteria will be applied for the key stakeholder representatives and leaders of delivery programs interviews: staff that are not directly involved with the management or activation of the Seniors Exercise Park or people who do not deliver/run programs/services using the outdoor equipment.

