##### AIM 1a—Primary impact measure of the implementation intervention

The number of older people (users) engaging in physical activity using the Seniors Exercise Park will be evaluated using periodic observation (the System for Observing Play and Recreation in Communities (SOPARC)). The SOPARC is a reliable and feasible instrument for assessing physical activity and associated contextual data in community settings [35]. It is based on momentary time sampling techniques, which systematically and periodically scan individuals and contextual factors within pre-determined target areas in parks. We will use a modified version of the SOPARC, which will record number of visitors, the gender and activity modes/types of people utilising the Seniors Exercise Park [22]. Additional data about the type of usage of the equipment by coding the interaction with the outdoor exercise equipment (i.e., ‘using equipment as intended’ or ‘playing/looking/sitting’ on the equipment) will also be collected [22, 36]. Systematic scans will be conducted over a 10-day period (including weekend) with a total of 14 scans as follows: every 30 min of all park visitors in the study area during early morning (07:30–10:30), mid-day (12:00–13:30) and late afternoon (15:00–17:30) [37]. Evaluation will take place monthly during the control period (Baseline), every 3 months during the implementation intervention phase and once during the three-month maintenance phase. In the event that there are missing scans (e.g. due to days with extreme weather conditions), these scans will be rescheduled to an equivalent day.

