### Secondary measures

#### Intercept survey with park visitors

##### Users’ physical and health characteristics

Face-to-face intercept surveys (15–20 min) will be conducted at baseline (pre-implementation B1, B2, B3), during the implementation framework (I1, I2, I3), and at the end of the maintenance follow up (M1). Data will be collected during the periodic observation (SOPARC) days. Intercept surveys will provide more in-depth information about Seniors Exercise Park users’ characteristics. The paper-based survey will include a set of questions across various domains similar to previous research [37, 40], as well as validated questionnaires (detailed below). The set of questions will include socio-economic and demographic characteristics of Seniors Exercise Park users (e.g., age group, gender, country of birth, marital status), if they are local residents or visitors, motivation to use the Seniors Exercise Park equipment, how often they visit the park area, social connectedness/engagement with other people at the park area, their general physical activity level and their leisure/recreation activity at the park, and general health and wellbeing. Socio-economic status will be estimated using postcodes to derive the Australian Socio-Economic Indexes for Areas (SEIFA) 2021 Index of Relative Socio-economic Advantage and Disadvantage, where the first and tenth SEIFA decile represents geographical areas with the greatest socioeconomic disadvantage and advantage respectively [41]. Self-reported social and health-care services utilisation (e.g., General Practitioner visits, hospitalisations) for the 3 months prior, as well as leisure activities and occupation details, will also be collected at each time point to provide relevant information for the economic evaluation.

The following validated questionnaires will be used as part of the survey:
*Health-related quality of life* will be assessed using the EQ-5D-5L [42]. The EQ-5D-5L comprises five dimensions (mobility, self-care, usual activities, pain/discomfort and anxiety/depression), as well as an overall self-rated health status (Visual Analog Scale (VAS) 0–100) where a higher score represents better health. The utility score will be used for the economic evaluation.

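### Aim 2 compares survey respondents, who must be 60 or over and speak English, with all local adults, so the comparison cannot show whether they resemble local older residents

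*Protocol article*

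**What the plan says.** In the protocol article, the statistical analysis for Aim 2 begins with summary statistics on users at each time point and then adds a comparison with an outside population: "Data will also be examined and reported relative to the adult general public, based on the distribution of age, marital status, and country of birth". The source of the comparator is given as "using Australian Bureau of Statistics census data for each local government area". The text states no age limit on the census population, no standardisation for age and no language restriction.

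The people being compared are defined elsewhere in the article:

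- The Inclusion criteria for the face-to-face survey are "1) adults aged 60 and over, (2) adults who are able to understand basic English and have conversational English". The Exclusion criteria mirror them: "1) participants who identify themselves as less than 60 years of age and (2) who are unable to understand basic conversational English".
- The section on users' physical and health characteristics places the demographic items in that survey: "socio-economic and demographic characteristics of Seniors Exercise Park users (e.g., age group, gender, country of birth, marital status".
- The observation tool covers all visitors, but the Aim 1a section describes it as a count "which will record number of visitors, the gender and activity modes/types of people utilising the Seniors Exercise Park". It lists neither marital status nor country of birth.
- The Study setting section gives the older share of the five council areas: it "ranges between 10.9% to 22% (people 60 years and over) and 7.4% to 17% (people 65 years and over").

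**The concern.** A comparison with census data is useful when the two groups could in principle have the same distribution. A difference then says something about who uses the parks or who answers the survey. Here they cannot match on age, because everyone under 60 is in the comparator and nobody under 60 can be in the sample.

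The problem carries over to the other two variables. Marital status depends on age (widowhood is the obvious example), and country of birth can differ between generations. Country of birth is also affected by the language criterion, which removes some people born overseas from the sample but not from the census figures.

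A group of respondents that mirrored local residents aged 60 or over exactly would therefore still look different from the stated comparator. The authors intend the results to inform scale-up, and this is the only planned comparison of respondents with the local population on these characteristics.

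**Working it through.** **The plan's own figure.** The only number stated for the surveyed group is its size. Per site, 8 + 34 + 12 = 54, and 54 × 6 = 324, which agrees with the sample size section. That figure is not in dispute. The census comparison has no stated significance level, power or margin, so no sample-size formula applies to it.

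**Inputs**

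- Share of respondents aged 60 or over: 100%, from the inclusion and exclusion criteria.
- Share of the areas' population aged 60 or over, p: 10.9% to 22%, from the Study setting section, read as a share of all residents.
- Adult share of residents, a: not given in the article. Assumed to be 70% to 80%.

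**Step 1. Share of adults aged 60 or over, q = p / a**

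| p | a = 0.80 | a = 0.70 |
|---|---|---|
| 10.9% | 13.6% | 15.6% |
| 22% | 27.5% | 31.4% |

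The range is about 14% to 31%.

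**Step 2. Gap forced by the entry rule, 1 − q**

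- Largest: 1 − 0.136 = 0.864, or 86 percentage points.
- Smallest: 1 − 0.314 = 0.686, or 69 percentage points.

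Without the assumption about a, using the stated shares directly, the gap is 1 − 0.22 = 0.78 to 1 − 0.109 = 0.891, or 78 to 89 points. Either way, more than two thirds of the comparator is in an age range that cannot enter the survey.

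**Step 3. Carry-over to marital status (illustration only).** Suppose respondents match local people aged 60 or over perfectly. Let w be the proportion widowed at 60 or over and v the proportion among younger adults. The all-adult proportion is q·w + (1 − q)·v, so the apparent difference is (1 − q)(w − v). The article gives neither w nor v. Assume w of 10% to 20% and v of 1%:

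- Smallest: 0.686 × (0.10 − 0.01) = 0.062.
- Largest: 0.864 × (0.20 − 0.01) = 0.164.

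On these assumed values, a perfectly representative sample would still appear to differ by about 6 to 16 points in widowhood.

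**Step 4. Country of birth.** The article gives no figures on language or birthplace by age, so the effect of the English criterion cannot be sized from it.

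**Step 5. After the change.** With the census comparator limited to residents aged 60 or over, both groups are 100% aged 60 or over and the forced gap is 0. The age limit then no longer drives any remaining difference in age within that group or in marital status. The English criterion would still affect country of birth.

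**The case against.** The strongest reply is that the wording is loose and the matter small. Comparing on the basis of an age distribution might mean comparing within age groups. The authors already work with local figures for ages 60 and 65 and over. The choice of census table is the kind of detail a condensed article can leave to a fuller document. The comparison is also descriptive and feeds no model.

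The last part stands: the usage model, the physical activity regressions, the sample size and the economic evaluation do not use it. The rest does not rescue the text. The article does not leave the population open; it names one, and it is not the surveyed one. Stratifying or weighting to the adult age distribution cannot help either, because there are no respondents below 60.

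Two stronger readings are tempting, and the article supports neither.

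- A reader might infer that the entry criteria produce all the differences that will be reported. That is certain only for the share aged 60 or over. Differences in marital status, in country of birth and in age within the group may also reflect who uses the parks and who agrees to be surveyed. The criteria distort these contrasts but are not shown to account for them entirely.
- A reader might infer that the study's assessment of Reach would be wrong. Table 3 measures Reach by the number of older people using the equipment (observation and app usage) and an audit of exercise programs. The census comparison is not among those measures, and the Aim 2 text does not attach it to Reach.

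**Conclusion.** The comparator is wrongly stated. As written, the comparison sets English-speaking respondents aged 60 or over against adults of all ages, and so cannot show whether respondents resemble local older residents. The forced gap in the share aged 60 or over is about 69 to 86 percentage points if adults are 70% to 80% of residents, which is an assumption. The knock-on effect of 6 to 16 points for widowhood is an illustration on assumed rates, and the language effect on country of birth cannot be sized from the article. The consequence is confined to one descriptive comparison. It should be corrected before the results are reported, but it does not touch the primary outcomes.

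**What to change.** In the Aim 2 analysis section, name census residents aged 60 or over in each local government area as the comparator in place of all adults, and state that the comparison is made within age bands. Add a sentence saying that the survey's English criterion limits what the country-of-birth comparison can show.

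Restricting the census group to people with comparable English is not advised. The article does not show that a census item matches the field judgement of conversational English. The restriction would also take non-English speakers out of the comparator, which could hide any shortfall among migrant groups.

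The cost is a change of wording and a different census extract. It needs no extra participants and no change to the survey.

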## Methodology

### Study objectives

Aim 1 – to evaluate the effectiveness of the implementation framework on increasing uptake and usage of the Seniors Exercise Park across six sites within five local government regions. Specifically, we will evaluate:
the number of older people engaged in physical activity utilising the Seniors Exercise Parksthe types of usage and uptake (e.g., organised programs, independent usage)the contexts and mechanisms (barriers/facilitators) influencing implementation.Aim 2 – to improve physical activity and wellbeing of older people using the equipment. Specifically, we will evaluate:the physical activity and wellbeing outcomes of older people utilising the equipmentolder people’s usage characteristics of the equipment (e.g., frequency, duration).Aim 3 – to evaluate the social return-on-investment when scaling the Seniors Exercise Park across multiple local government areas.

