### Study design

All procedures involved in this trial will be conducted in compliance with the National Statement on Ethical Conduct in Human Research and the Australian Code for the Responsible Conduct of Research. The study was approved by the Monash University Human Research Ethics Committee, Melbourne Australia (Project ID: 35502). The study was designed according to the Strengthening The Reporting of Observational studies in Epidemiology (STROBE) statement [23]. STROBE check list is provided as an additional file.

The ENJOY IMP-ACT study is an implementation research project employing a hybrid II implementation-effectiveness pre-post mixed method design [24]. We will implement and evaluate the implementation intervention, process and impact using the Reach, Effectiveness, Adoption, Implementation, and Maintenance (RE-AIM) Framework [25] and our adopted logic model (see Fig. 1). Six sites in Victoria, including two regional sites, will participate in the study with a pragmatic staggered commencement. Each site will have a 3-month control period followed by 9-months implementation intervention (TERM framework intervention: Training, Engagement, Resources development, Marketing and promotion), and a maintenance phase (3 months) (Fig. 2). The pre-post design is a pragmatic real-world design where all local governments will receive the implementation intervention framework. A control period will act as the waiting list ‘control arm’.

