### Assessments

#### Outcome measures

##### Primary outcomes

The primary impact measures of the implementation framework intervention are: (1) *the number of older people* who engage in physical activity using the Seniors Exercise Park (irrespective of usage mode: e.g., if via group-led programs or independent usage), and (2) *the physical activity level of users*.

Following the hybrid II design, we will evaluate the impact of the intervention and the potential contextual factors (community/organisational level factors) that may influence implementation (barriers/facilitators) of the TERM framework. In addition, we will evaluate older people’s quality of life, wellbeing and self-reported health care utilisation. The RE-AIM model [25] (see measures described in Table 3) and our logic model will guide the project evaluation (Fig. 1).

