##### Sample size calculation for the intercept surveys

Sample size calculations for the intercept surveys as part of aim 2 are based on the expected number of older people who will complete the survey using data from our previous project [22]. We observed 10 older people using the Seniors Exercise Park in a typical week (prior to formal promotion of the newly installed park). We hypothesised that the implementation intervention (TERM) will result in *at least* a twofold increase in the number of older people using equipment at the completion of the intervention phase (I3) compared to baseline (B1,B2,B3), with a 20% attrition rate (proportion of people refusing to be interviewed) during the maintenance phase (M1). Assuming 25% will decline to participate or have previously completed the survey [40], we will aim for a total of 54 intercept surveys (8 at baseline; 34 across I1-I3 and 12 at M1) per site, with an overall sample of 324 interviewees across the six sites. Each data collection period will include an observation period of 10 days (instead of a typical 7-day period as commonly used [35]). Increasing the number of observations days to 10 days will enhance opportunities for the research team to recruit more older visitors to complete the intercept surveys to meet the targeted sample size.

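### For the physical activity primary outcome, the only stated significance criterion concerns differences between sites; no test or contrast is named for the overall change from baseline that Aim 2 asks about

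*Protocol article*

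**What the plan says.** The Primary outcomes section begins "The primary impact measures of the implementation framework intervention are" and lists two: the number of older people using the park, and the physical activity level of users. Study objectives gives Aim 2 as "to improve physical activity and wellbeing of older people using the equipment". Under Study design, "all local governments will receive the implementation intervention framework", and each site's own 3-month control period serves as the comparator.

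The Aim 2 analysis section then makes two statements. The first gives the model: "Linear and logistic regression models (with main effects for site, time-point, season and their interaction) will be used to examine the impact of the implementation". The outcome of that model is how active users are, and the section labels it as primary. The second gives the significance criterion: "Statistical significance of the interaction term will be used to determine if the outcome varied between sites at each intervention time point". The time points meant are the three intervention waves and the maintenance wave, each judged against how the sites differed at baseline.

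The sample size section plans "54 intercept surveys (8 at baseline; 34 across I1-I3 and 12 at M1) per site, with an overall sample of 324 interviewees". It gives no significance level, power, effect size or SD for physical activity. The Intercept surveys section allows the same person to be surveyed more than once during the intervention period.

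**The concern.** All six sites are treated, so site is not a treatment comparison. The effect that Aim 2 needs is the change from B1-B3 to the intervention period, taken across sites. A site-by-time-point interaction answers another question: whether that change differs from site to site. It is the only term to which the section attaches statistical significance.

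The time-point term does not settle the matter as written. Once the interaction is in the model and ordinary reference coding is used, each time-point coefficient is the change at the reference site alone. A change averaged over the six sites has to be requested, and the section does not request it. Nor does it say whether I1, I2, I3, I1-I3 pooled or M1 is the primary comparison. The Aim 1 model at least names an intervention term; the Aim 2 model names none.

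Two things are at stake. If an analyst took the stated test as the test of effect, a benefit shared by all sites would be missed. If the contrast stays open, it could be chosen after the results are seen.

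**Working it through.** **Inputs from the protocol.** Per site: 8 baseline, 34 intervention and 12 maintenance surveys; six sites; 10 users in a typical week before promotion; at least a twofold rise by I3; 25% declining or already surveyed; 20% attrition at M1.

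**Reproducing the plan's figure.**
- Baseline: 10 × 0.75 = 7.5, rounded to 8.
- I1-I3: (10 + 15 + 20) × 0.75 = 33.75, rounded to 34. The 10/15/20 build-up is an assumption; a flat 20 per wave would give 45.
- M1: 20 × 0.8 × 0.75 = 12.
- Total: 8 + 34 + 12 = 54 per site, and 54 × 6 = 324. This agrees with the protocol.

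**Assumptions for what follows.** Two-sided 5% level, 80% power (multiplier 1.96 + 0.84 = 2.8), outcome SD of 1, independent responses, season ignored.

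**Detectable differences.** I3 surveys per site are taken as 20 × 0.75 = 15.
- Pooled change, I1-I3 against baseline (6 × 34 = 204 against 6 × 8 = 48): 2.8 × √(1/48 + 1/204) = 2.8 × 0.160 = 0.45 SD.
- Pooled change, I3 alone (6 × 15 = 90 against 48): 2.8 × √(1/48 + 1/90) = 2.8 × 0.179 = 0.50 SD.
- Change at one site, I3 against baseline, which is what a reference-coded time-point coefficient gives: 2.8 × √(1/8 + 1/15) = 2.8 × 0.438 = 1.2 SD.
- Difference between two sites in that change: 2.8 × √(2 × (1/8 + 1/15)) = 2.8 × 0.619 = 1.7 SD.
- If I3 yields 12 per site instead of 15, the last two become 2.8 × √(1/8 + 1/12) = 1.3 SD and 1.3 × √2 = 1.8 SD.

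**What each test responds to.** A simulation with 20,000 replicates per scenario used 6 sites and 8, 11, 11, 12 and 12 surveys per site at baseline, I1, I2, I3 and M1 (324 in all). The pre-post contrast compares baseline with all later periods, M1 included. The time-point test comes from a model with site and time-point but no interaction. Rejection rates under an equal shift at every site after baseline:

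| Shift at every site | Site-by-time-point interaction (20 df) | Time-point (4 df) | Pre-post contrast (1 df) |
|---|---|---|---|
| 0 | 5% | 5% | 5% |
| 0.2 SD | 5% | 14% | 25% |
| 0.3 SD | 5% | 29% | 48% |
| 0.5 SD | 5% | 72% | 89% |
| 0.8 SD | 5% | 99% | 99.9% |

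A hand check of the 89%: the standard error is √(1/48 + 1/276) = 0.156; 0.5/0.156 = 3.20; 3.20 − 1.96 = 1.24, which gives 89%.

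In the opposite case, with +0.8 SD at three sites and −0.8 SD at the other three, the mean change is zero. The interaction then rejects in 88% of replicates and the pre-post contrast in 4%. The stated test and the Aim 2 question can therefore give opposite answers.

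**The case against.** The strongest reply is that the section has two sentences with two purposes. The first says the models examine the impact of the intervention and includes a time-point main effect. The second gives the interaction its proper task, which is to look for variation between sites. A reader might infer that the interaction decides whether the intervention worked, so that a uniform benefit would be reported as no effect. The protocol says neither, and that reading is not supported. It is equally too strong to say that nothing in the model could answer Aim 2, because a time-point effect can carry a uniform change. The reference-site problem is a matter of coding: effect coding, or marginal means averaged over sites, would recover the average change from the same model. All of this stands.

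The reply also notes that a condensed article may leave contrast coding to an analysis plan. That would answer a complaint about silence. Here the article does state an inferential criterion for a primary outcome, and the criterion addresses a different question from the aim. That part of the reply does not remove the point.

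Two limits on the figures are fair. The 1.7 SD describes a comparison of two sites at I3, not the power of the joint interaction test. The calculations also treat responses as independent although repeat surveys are allowed during the intervention. Repeats within the intervention period would reduce the information there, while the same people appearing before and after could sharpen the comparison, so the net direction is unknown.

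**Conclusion.** The point holds as a mismatch between the stated test and the aim. Significance is tied only to between-site variation, while Aim 2 and the design call for the overall change from baseline. The interaction rejects at its nominal 5% whatever the size of a uniform change. The planned surveys could detect a pooled change of about 0.45 SD, but only about 1.2 SD at a single site and about 1.7 SD between two sites' changes. A non-significant interaction would therefore say little about consistency.

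The 5% result for the interaction follows from what that test measures and does not depend on the sample size. The SD figures rest on independence, a two-sided 5% level, 80% power and an assumed 15 surveys per site at I3.

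**What to change.** Add one sentence to the Aim 2 analysis. It should state the primary test as a single pre-specified contrast of the intervention period (either I3 or I1-I3 pooled, chosen now) with B1-B3 pooled, averaged over the six sites and reported with its estimate and 95% CI. The contrast can be a marginal one from the stated model or come from a model without the site-by-time-point interaction; dropping the interaction is not essential. The analysis should allow for people surveyed more than once, which requires repeat respondents to be identifiable.

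Keep the interaction as a secondary heterogeneity analysis, say which of the possible interactions is meant, report site-specific changes with intervals, and do not read non-significance as consistency. The cost is a wording change and, if not already planned, a means of linking repeat surveys. No additional surveys are needed.
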